## Abstract

The World Health Organization and the International Confederation of Midwives emphasize the importance of accreditation to enhance quality in midwifery education. In midwifery education programmes, internal self-assessments are used to meet accreditation criteria. However, research on this topic is scarce. Therefore, this paper describes how we plan to conduct an evaluation of an internal quality assurance process in midwifery education aimed at achieving national accreditation standards in Bangladesh. This study has a longitudinal exploratory design and will be guided by the principles of process evaluation of complex interventions. An internal quality assurance self-assessment intervention will be introduced at 31 private and public education institutions in Bangladesh. To ensure a sustainable implementation, the Plan-Do-Study-Act cycle will be introduced. Data will be collected using self-administered questionnaires and focus group discussions with midwifery faculty and final-semester students. Descriptive statistics and regression models will be performed for the quantitative data, and the qualitative data will be analysed using content analysis. It is anticipated that, without internal quality assurance of midwifery education programmes, accreditation alone is unlikely to enhance quality. We aspire for this research project to illustrate a process that the midwifery institutes can implement themselves for sustainable transformation towards high-quality midwifery education in countries where such internal quality assurance processes have not yet been integrated into the education system.

**Trial registration**: The study was registered retrospectively with the ISRCTN registry on 26 August 2024. The registration number is: ISRCTN14492910.

## Background

In midwifery education programmes in several high-income countries, recurrent self-assessments are conducted to ensure a learning environment in which the content of programmes, learning opportunities, and facilities effectively meet education goals [1]. These self-assessments offer valuable feedback and suggestions for enhancing quality in education programmes in preparation for the establishment of formal accreditation [1–3]. Both the World Health Organization and the International Confederation of Midwives emphasize the critical role of accreditation in improving the quality of midwifery education [4–6]. Despite this emphasis, there is a notable gap in research on the effectiveness of self-assessments for continuous quality improvement in midwifery education, particularly before and after formal accreditation. This highlights the need to scientifically evaluate internal quality assurance self-assessments for achieving national accreditation standards in midwifery education programmes. In our study, Bangladesh is used as an example.

The International Confederation of Midwives has established education standards to strengthen midwifery globally by promoting quality education programmes that prepare midwives in line with the International Confederation of Midwives definition of a midwife [6]. These standards consist of six categories: i) Programme governance, ii) Faculty, iii) Students, iv) Midwifery programme and curriculum, v) Resources, and vi) Quality improvements. These standards are grounded in the best available evidence and serve as a benchmark for minimal achievement in midwifery education. The standards offer a structured approach for developing, implementing, and assessing programme quality while ensuring alignment with regulatory requirements [6]. By adhering to these standards, midwifery education programmes can demonstrate accountability to the public and adapt to national and local workforce demands. In essence, these standards encompass criteria such as programme duration, entry-level skills, core competencies, educator qualifications, and ongoing competency maintenance for fully qualified midwives. The International Confederation of Midwives global standards for midwifery education [6] can be used to develop an internal quality education assurance process, such as a self-assessment at an education institution, while at the same time taking the national context into consideration.

Less than half of the world’s countries have an accreditation system for midwifery education, and it is evident that midwifery education programmes, particularly in low-income countries, do not fully meet accreditation standards. Accreditation formally acknowledges procedures aimed at ensuring that education programmes adhere to national established standards, thereby enabling graduates to attain the agreed-upon minimum level of competence [7,8]. Research on accreditation’s impact on education quality exists [8–11], but there is a lack of studies on continuous improvement such as self-assessments in midwifery education before and after accreditation.

Investment in midwifery education by the government of Bangladesh over the past decade [12] has been aimed at improving maternal and newborn mortality and morbidity, yielding positive results [9,13–18]. However, progress has stagnated [19]. To meet the Agenda 2030 target of reducing the maternal mortality ratio to less than 70 deaths per 100,000 live births, the government has initiated measures for an internal quality assurance self-assessment process for midwifery education programmes, in addition to the national accreditation system. This paper describes how we plan to conduct an evaluation of the internal quality assurance process in midwifery education aimed at achieving national accreditation standards in Bangladesh. The specific aims are to:

Evaluate to what extent education standards are met in the internal quality assurance process at midwifery education institutions.

Determine the effectiveness of the internal quality assurance process in producing competent and confident educators and midwives.

Identify contextual factors influencing the internal quality assurance process to reach national accreditation standards for midwifery education.

The term ‘quality assurance’ is used in this paper to describe all activities within the recurrent improvement cycles.

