### Hypothesis

We hypothesize that implementing an internal quality assurance process will improve the quality of midwifery education programmes, producing competent and confident educators and midwives and thereby meeting national accreditation standards.

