## Methods

### Research design

The evaluation of the internal quality assurance process for midwifery education will use a longitudinal exploratory design guided by the principles of process evaluations of complex interventions [20]. This includes a description of an intervention and contextual factors that may affect the implementation process of the intervention, what is delivered (fidelity, dose, adaptations, and reach), the mechanisms of the impact that influence the intervention activities (responses, mediators, unexpected pathways, and consequences), and the outcomes of the intervention [20]. For details, see Figure 1.

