#### Setting

Midwifery education in Bangladesh is currently delivered at 147 institutes (60 public, 87 private) across the country, consisting of 60% clinical practice and 40% theory leading to a diploma degree after three years of study. Each of these programmes admits 25 to 50 students annually, attracting students from rural and urban areas. The educators hold a PhD or master’s degree, either in Sexual Reproductive and Perinatal Health, Hospital Management, Women’s Health, Nursing, or Public Health [11,14,21]. The internal quality assurance process will be initiated in 31 of the 147 public and private education institutions selected by the government of Bangladesh. The United Nations Population Fund in Bangladesh and the Swedish Development Cooperation Agency support these institutions in strengthening midwifery education and services in the districts where they are located.

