#### The internal quality assurance process intervention for midwifery education

The intervention consists of an internal quality assurance process to be integrated in education institutions to enhance the quality of midwifery education. Through a recurrent self-assessment, the faculty assess their respective education programmes against national and international standards [22]. The faculty within the midwifery education programmes internally analyse the achievements of the self-assessment, indicating which standards are met, partially met, and unmet and what changes need to be prioritized in the next cycle. Based on the yearly self-assessment findings, the faculty make a recurrent activity plan. The learning from one assessment guides the plan that follows [23].

The implementation strategies include the following steps:

Update an existing tool to become a quality assurance assessment tool. The updated tool will be aligned with the new International Confederation of Midwives education standards [6] and the Bangladeshi accreditation standards for midwifery education programmes [9,11,17].

Train quality assurance task force committee members, consisting of midwifery educators (*n* = 21) selected by the government, representing both public and private education institutions. They will be trained on the quality assurance assessment tool during a four-day workshop. Upon completion, they will collect baseline data from all 31 sites.

Implement the Plan-Do-Study-Act (PDSA) cycle at all 31 institutions. The PDSA cycle is a four-step approach commonly used for quality improvement [23]. Through this approach, education institutions can ensure that their midwifery programmes meet education standards, fostering an environment of continuous improvement in midwifery education. The following steps will be applied:

Initially, the faculty members, such as educators, clinical supervisors, midwifery students, and library, computer lab, and clinical simulation managers, will conduct a yearly self-assessment of their education programmes against education standards. Following the self-assessment, an internal analysis of the findings will identify which areas require prioritization for improvement. This will provide a clear understanding of the changes needed to meet the standards.

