## Discussion

Introducing an internal quality assurance process in Bangladesh can potentially transform midwifery education sustainably towards higher quality [22,29]. In Bangladesh, the Ministry of Health, the Bangladesh Nursing and Midwifery Council, and the Directorate General of Nursing and Midwifery (DGNM) are responsible for ensuring the quality of midwifery education. Our research project supports these entities with scientific data and new knowledge which will be used for disseminating the internal quality assurance process across all midwifery education institutions in Bangladesh [22]. It is expected that this new knowledge will contribute to the common understanding of quality assurance for learning and teaching across the institutions.

While the Bangladeshi government has initiated the national accreditation system, they have at the same time initiated an internal quality assurance process in midwifery education. Introducing the internal quality assurance process in parallel with the accreditation allows the Bangladeshi education system to demonstrate quality and increase transparency, thus supporting the building of mutual trust and better recognition of the midwifery programmes. In contrast, introducing accreditation alone could result in the closure of education programmes that may not meet the accreditation standards [11], leaving students without education and the country without enough midwives. Therefore, it can be argued that an internal quality assurance process must be implemented in parallel with continuous improvement cycles to meet national accreditation standards before the national accreditation reviews.

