### Impact of the research

#### At the policy level

Accreditation aims to ensure that education programmes achieve a minimum level of competence. Our research findings can demonstrate the usefulness of establishing an internal quality assurance process for sustainable transformation towards high-quality midwifery education in countries where such a process has not yet been integrated into the education system. This study could further provide guidance for policy- and decision-makers in designing a quality assurance process at the institutional level in collaboration with midwifery faculty.

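### Aim 2 and the hypothesis claim that the process produces competent educators and midwives, but an uncontrolled baseline-endline design with self-rated competence cannot support that claim.

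*Protocol article*

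**What the plan says.** The causal claim appears in several places in the protocol article.

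- Background, second specific aim: "Determine the effectiveness of the internal quality assurance process in producing competent and confident educators and midwives".
- Hypothesis: "implementing an internal quality assurance process will improve the quality of midwifery education programmes, producing competent and confident educators and midwives", and in this way meeting national accreditation standards.
- Quantitative data: the educator tool and the student tool are each introduced as the means of judging how effective the process is in producing competent and confident educators and midwives.
- At the policy level: "Our research findings can demonstrate the usefulness of establishing an internal quality assurance process for sustainable transformation towards high-quality midwifery education".

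The design is described as follows.

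- Research design: the study "will use a longitudinal exploratory design guided by the principles of process evaluations of complex interventions".
- Setting: the process starts in "31 of the 147 public and private education institutions selected by the government of Bangladesh". On the same sites: "The United Nations Population Fund in Bangladesh and the Swedish Development Cooperation Agency support these institutions in strengthening midwifery education and services".
- Intervention section: "Implement the Plan-Do-Study-Act (PDSA) cycle at all 31 institutions". The task force collects baseline data from all 31 sites.
- Discussion: "Introducing the internal quality assurance process in parallel with the accreditation" is presented as a strength of the approach.
- Quantitative data: both competence tools are self-assessments (97 items for educators, 230 for students), given once at the start and once at the end of the study.
- Data analysis: descriptive statistics, principal component analysis, chi-square tests of scores against socio-demographic variables, correlation of confidence with competence, and regression models chosen from those results.

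**The concern.** To say that a process produced competence, one needs some account of what would have happened without it. The design offers none. Every studied site receives the process, and the only contrast in time is baseline against endline. Accreditation and agency support, both named in the article, are directed at the quality of midwifery education in the same places. Cohort differences and national trends come on top. Any of these could move the scores in either direction.

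The outcome adds a second gap. The intervention trains sites to judge themselves against standards, so the way people rate themselves may change while their competence does not. Ratings could rise with familiarity or fall as people become more critical.

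What is at stake is the conclusion. The Discussion says that the findings will be used in extending the process to all midwifery institutions in Bangladesh. If aim 2 stands as worded, a rise in self-ratings invites the reading that the process works, and an absence of change invites the opposite. The design supports neither.

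**Working it through.** **1. The document's own figures.** The article has no power calculation, effect size or standard deviation to reproduce. Its student count does reproduce: 31 sites × 25 students = 775 and 31 × 50 = 1550, as stated. Institutes outside the study: 147 − 31 = 116.

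**2. Claim against design.**

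| What an effectiveness claim needs | What the article describes |
|---|---|
| A comparator or an unexposed period | All 31 sites receive the process; none of the other 116 institutes is used; no staggered start is described |
| Separation from concurrent influences | Agency support at the same sites; accreditation in parallel |
| A measure of competence | Self-assessment by educators and by final-semester students |
| An estimate of the effect | The named tests relate scores to socio-demographics and confidence to competence |

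If endline falls a year or more after baseline, as the yearly cycles imply, the final-semester students at the two time points are different people. Change within a student could then not be estimated either.

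**3. Illustration of false attribution at site level.** All inputs except n = 31 are assumed. Suppose that the process has no effect, that mean site scores drift by d (in SDs of the site-level change), and that a two-sided paired t-test at 5% is applied. The test statistic follows a noncentral t distribution with 30 degrees of freedom and noncentrality d√31; the critical value is 2.042.

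| Drift d (SD) | d√31 | Probability of a significant change |
|---|---|---|
| 0.1 | 0.56 | 8% |
| 0.2 | 1.11 | 19% |
| 0.3 | 1.67 | 37% |
| 0.5 | 2.78 | 77% |

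**4. The same question at student level.** Take two independent cohorts of n students in 31 clusters. The variance of the difference is 2 × [(1 − ICC)/n + ICC × (1 − CAC)/31], where ICC is the intracluster correlation and CAC the correlation of a site's mean between waves. The assumed ranges are ICC 0.02 to 0.10 and CAC 0 to 0.8, with full response.

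- Shift of 0.1 SD: from 19% (n = 775, ICC 0.10, CAC 0) to 73% (n = 1550, ICC 0.02, CAC 0.8).
- Shift of 0.2 SD: from 57% to above 99% over the same settings.

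For given ICC and CAC, the larger sample gives the higher probability of a false finding, so more students do not cure the problem.

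**5. What an internal dose contrast could do.** With 31 sites, the correlation detectable with 80% power at two-sided 5% is tanh[(1.96 + 0.84)/√(31 − 3)] = tanh(2.80/5.29) = tanh(0.529), about 0.48.

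**The case against.** The strongest reply is that the study is openly exploratory and is a process evaluation. Aim 3, the attention to context, fidelity, dose and mechanisms, and the fourteen focus groups (ten institutional, four with the task force) are its stated means of examining context. Much of the impact language is cautious, and the scores are called self-assessed in the analysis section. This softens the point but does not remove it. The exploratory label sits beside an aim, a hypothesis and two tool purposes that keep effectiveness wording. Focus groups can explain context and mechanism, but they give no counterfactual. Nor is this a detail left to an unseen analysis plan, since an analysis plan cannot add a comparator to the design described.

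Several objections to stronger readings do stand.

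- A reader might infer that all sites start simultaneously. The article prints no roll-out calendar; it says only that all 31 receive the process and describes no unexposed period.
- A reader might treat accreditation and agency support as wholly new forces arriving between baseline and endline. The article gives no start date for the support and elsewhere refers to accreditation as already existing, so how much new pressure falls within the study period is unknown.
- A reader might settle on one false-attribution figure, such as 77%. It depends on an assumed drift, and the paired test is not among the analyses named.
- A reader might conclude that the authors will report any rise as an effect. The article does not say so; the risk lies in the wording of the aim.

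**Conclusion.** The point holds as a mismatch between claim and design. Aim 2, the hypothesis, the stated purposes of the two competence tools and the policy claim go further than an uncontrolled baseline-endline comparison of self-ratings can support. The conclusion rests on the article's own text and needs no numerical assumption. Bias from background change equals that change in full, but its size here is unknown. The illustrative 8% to 77% for site-level drifts of 0.1 to 0.5 SD shows how strongly the answer depends on an unknown, and is not an estimate for this study. Aim 1 (how far standards are met) and aim 3 (contextual factors) are not touched by this point.

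**What to change.** Reword aim 2, the hypothesis, the purposes of the educator and student tools under Quantitative data, and the claim under At the policy level. A possible wording for aim 2 is: to describe change in self-assessed competence and confidence of educators and final-semester students during introduction of the internal quality assurance process, alongside national accreditation and donor support. Add one sentence stating that change will not be attributed to the process alone.

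The cost is a more modest claim. No new sites, staff, visits or data are needed.

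Optionally, a site-level association of score change with delivered dose may be added, labelled exploratory. It could pick up only a fairly strong correlation (about 0.48 for 80% power). It stays open to confounding, because accreditation effort or donor support may raise both dose and scores, and to shared reporting bias where dose and scores are both self-reported. It would not separate the process from the other influences and is no substitute for the rewording. If a false-attribution probability is quoted anywhere, show it as an assumed range.

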### Hypothesis

We hypothesize that implementing an internal quality assurance process will improve the quality of midwifery education programmes, producing competent and confident educators and midwives and thereby meeting national accreditation standards.

## Methods

### Research design

The evaluation of the internal quality assurance process for midwifery education will use a longitudinal exploratory design guided by the principles of process evaluations of complex interventions [20]. This includes a description of an intervention and contextual factors that may affect the implementation process of the intervention, what is delivered (fidelity, dose, adaptations, and reach), the mechanisms of the impact that influence the intervention activities (responses, mediators, unexpected pathways, and consequences), and the outcomes of the intervention [20]. For details, see Figure 1.

**Figure 1. f0001:**
[figure not shown]
Key functions of process evaluation and relations among them as described by Moore et al. [20].

#### Setting

Midwifery education in Bangladesh is currently delivered at 147 institutes (60 public, 87 private) across the country, consisting of 60% clinical practice and 40% theory leading to a diploma degree after three years of study. Each of these programmes admits 25 to 50 students annually, attracting students from rural and urban areas. The educators hold a PhD or master’s degree, either in Sexual Reproductive and Perinatal Health, Hospital Management, Women’s Health, Nursing, or Public Health [11,14,21]. The internal quality assurance process will be initiated in 31 of the 147 public and private education institutions selected by the government of Bangladesh. The United Nations Population Fund in Bangladesh and the Swedish Development Cooperation Agency support these institutions in strengthening midwifery education and services in the districts where they are located.

